### Data Collection

#### Procedure

At enrollment, RAs will complete the Injury Profile Form and Research Methods Feasibility Form. They will also document opioid and non-opioid consumption over the last 3 days and distribute the BPI. During program delivery, the trauma nurse and the pharmacist will record information on the feasibility of the program and the attrition rate via the Program Feasibility Evaluation Logbook and the Research Methods Feasibility Data Form. A RA will contact participants in the experimental and control groups over the phone, or meet them at the outpatient clinic, to document their opioid and non-opioid consumption and complete the BPI questionnaire, at 6 and 12 weeks after randomization. They will also contact participants’ community pharmacies to obtain information on opioid and non-opioid delivery at both time periods.

### Data analysis

#### Feasibility and acceptability

To determine the feasibility of TOPP-Trauma, the rates of program components actually delivered to participants, the challenges faced during program delivery and the pain self-management strategies applied by participants will be calculated. Moreover, mean time required for the delivery of TOPP-Trauma sessions will be computed.

Regarding the Feasibiliy of Research Methods, the following descriptive data will be obtained: 1) the number of patients screened to participate in the study, of eligible patients, and of participants included, 2) the number of inclusion and exclusion criteria that were not met, 3) the mean time required to obtain consent, to screen participants for their chronic consumption risk, and to obtain baseline data, 3) the percentage of participants who accept to be randomized to either the experimental or control group, 4) the dropout rate relative to each program session and outcome measure time point, 5) the mean time between expected dates for questionnaire completion and actual completion, and 6) the recall rates for questionnaire completion [54].

Mean scores will be calculated with regard to data collected with the TAP Questionnaire. Answers to open-ended questions, pertaining to the modifications required to improve intervention acceptability, will be group into categories according to core themes identified during content analysis.

#### Potential efficacy of the program

All outcome data will be analyzed via an intent-to-treat approach. Mean values will be calculated to determine the direction and amplitude of the differences within and between groups on the outcome measures over time. The percentage of opioid-free participants, of participants taking ≥2 doses per day of each class of non-opioid analgesic, and of participants with mild pain intensity and pain interference with activities (i.e., < 4 of a 0–10 Numerical Rating Scale) [64] will be computed. Data will be analyzed at baseline, 6 weeks and 12 weeks.

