**Methods:**

A 2-arm pilot randomized controlled trial (RCT) will be conducted in patients presenting a high risk for chronic opioid consumption. Fifty participants at high risk for chronic consumption of opioid will receive either TOPP-Trauma or an educational pamphlet. The feasibility assessment of TOPP-Trauma will be based on the ability to provide its components as initially planned. Several parameters will be evaluated to determine the feasibility of the research methods, including the adequacy of the sampling pool, the dropout rate, and the ease of data collection. The morphine equivalent dose (MED) per day between both groups will be measured at 6 and 12 weeks. Pain intensity and pain interference with activities will also be evaluated at the same time points.

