#### Program Content

The biopsychosocial model of pain [39] emphasizes that disorders, such as pain, result from the dynamic interaction between biological, psychological, and social factors which may perpetuate and worsen pain. This model was influenced by the neuromatrix theory of pain [40, 41]. According to this theory, pain is the consequence of an output from a widely distributed brain neural network, impacting the biological and psychological dimensions of pain. The social dimension (e.g., daily living activities, environmental stressors) can trigger additional biopsychological reactions, thus contributing to the vicious circle of nociception, increased pain intensity, distress, and disability [42]. Hence, the biopsychosocial model of pain highlights the need to address pain management with multimodal strategies, in order to foster minimal opioid use.

TOPP-Trauma will focus on the same self-management behaviors promoted in iPACT-E-Trauma. In addition, counseling on opioid tapering and the use of alternative pain management strategies, as well as continued monitoring of opioid intake, will be provided. Recommendations on opioid tapering will be based on the adequacy of pain relief (pain intensity < 4/10 and pain mildly or not interfering with daily living activities). A dose reduction of 25% per day will be suggested at each session, until opioid cessation or until patients chronically prescribed opioids reach their target maintenance dose, as per guidelines on acute pain management [43].

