#### Feasibility and acceptability

A Program Feasibility Evaluation Logbook will make it possible to collect program feasibility data (Table 3) [58]. The Program Feasibility Evaluation Logbook will detail information on the program components that need to be delivered in each session, the pain self-management strategies applied by participants between sessions, the appropriateness of the physical environment in which the program is delivered, the time dedicated to adequately deliver the program and answer patient questions, and the challenges faced when providing the program.

**Table 3 Tab3:** Variables to assess the feasibility of the intervention and the research methods

Variables	Indicators
*Intervention feasibility*	
1- The possibility to deliver the intervention as planned 2- Participants adhering to the intervention	- Provision of ≥80% of planned components of each in-presence session and of the overall intervention [59].
	- Session duration (sessions 1 to 6: 15 min).
	- Challenges faced during session delivery.
	- Attendance to ≥80% of sessions by participants [59].
	- Involvement in intervention activities and implementation of recommended self-management ≥80% behaviors by participants [59].
*Research methods feasibility*	
1- Adequacy of the sampling pool and recruitment time 2- Ease of screening 3- The possibility of applying randomization procedures as planned 4- Attrition rate in experimental and control groups 5- Ease of data collection procedures	- Obtaining consent from ≥80% of patients approached to participate in the study.
	- Percentage of eligible patients who were included in the study. - Patient’s reasons for refusal to participate in the study.
	- Difficulties in obtaining patients’ consent.
	- Recruiting study sample (i.e., 50 participants) in ≤9 months [31].
	- The time required to screen participants relative to recruitment.
	- The time required to obtain consent and baseline data relative to recruitment.
	- Eligibility criteria not limiting the pool of participants by ≥50% [32].
	- Reasons for ineligibility.
	- Difficulties when applying the randomization procedures.
	- Patient acceptance to randomization, either to the treatment or control group ≥80% of the time [32].
	- Attrition rate in experimental and control groups, i.e., ≤ 20% [60].
	- Percentage of questionnaires completed in full.
	- Pattern and rates of non-answered questions at each time measure.
	- Mean time required to complete the outcome questionnaires.

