### Variables and Measurement Tools

#### Morphine equivalent dose/day

Opioids taken by participants will be measured by calculating the total morphine equivalent dose (MED) per 24 h, as recommended for studies on the consumption of opioids, using the appropriate conversion methods [61, 62]. Participants will be asked to self-report their opioid use for the last three days and the day associated with the highest MED will be retained. The MED/day will be measured at 6 weeks after the beginning of TOPP-Trauma, since some studies found that a great proportion of trauma patients do not use opioids beyond this period of time [22], as well as at 12 weeks after initiating the intervention. The medical file will be consulted to determine the highest MED over three days before participant randomization, as part of baseline assessment. A pharmacist, blinded to patient allocation, will compute the MED per day.

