### Sample Size

The pilot study was not designed for adequate statistical power but to test the feasibility and potential efficacy of the program [44]. To reach these aims, we estimate that a total of 50 participants should be randomized into each group (experimental and control). This sample size is realistic considering the number of trauma patients admitted in the center where the study will be conducted.

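### Direction of the opioid effect is read from mean MED/day, whose sign one or two participants can set at about 25 per arm; the planned opioid-free percentage has no stated role in judging it

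*Protocol article*

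**What the plan says.** The section on potential efficacy in the protocol article gives means the task of settling direction and size: "Mean values will be calculated to determine the direction and amplitude of the differences within and between groups on the outcome measures over time". The sentence after it adds "The percentage of opioid-free participants", to be computed at baseline, 6 weeks and 12 weeks. It does not say what that percentage contributes to judging direction, or what is concluded if it and the mean disagree.

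The article also describes what the MED/day data will look like:

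- **Many zeros.** The MED section justifies the 6-week measurement by noting that "a great proportion of trauma patients do not use opioids beyond this period of time". The Background puts use beyond 12 weeks at no more than 35% of trauma patients.
- **A possible upper tail.** Pre-injury opioid use is one of the qualifying risk factors under Eligibility Criteria. Under Program Content the taper runs to cessation or "until patients chronically prescribed opioids reach their target maintenance dose". The highest of three days is the value kept.

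The sample size is given in two ways. The abstract has "Fifty participants at high risk for chronic consumption of opioid will receive either TOPP-Trauma or an educational pamphlet", and Table 3 has "Recruiting study sample (i.e., 50 participants) in ≤9 months". The Sample Size section has "we estimate that a total of 50 participants should be randomized into each group (experimental and control"). The first two give about 25 per arm if allocation is 1:1, which the article does not state. The third gives 50 per arm.

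**The concern.** The mean of a variable with many zeros and a long right tail is governed by the few largest values. At this sample size, the sign of the difference in mean MED/day may reflect which arm happened to receive one or two high-dose participants, and not what happened to most participants.

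Two things depend on it. The third objective is to describe potential efficacy. The Discussion says the pilot will supply an adequate estimate of group differences in opioid consumption on which a full trial can build. A sign set by one participant would be a poor basis for choosing that trial's endpoint or effect size. The opioid-free percentage could show the problem, but without a stated role a reader may choose whichever summary looks better.

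**Working it through.** The article gives no MED distribution, no share or dose of maintenance users, and no effect size, so there is no planned figure to reproduce. Every distributional input below is an assumption.

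**1. Influence of one participant.** A participant at dose D shifts an arm mean by D/n. At n = 25: 90/25 = 3.6, 120/25 = 4.8 and 200/25 = 8.0 mg/day.

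**2. Size of the contrast.** Take 35% still using in the control arm (the Background's upper figure) and an assumed 20% under TOPP-Trauma, with users averaging 20 to 30 mg/day. The difference is 0.15 × 20 = 3.0 to 0.15 × 30 = 4.5 mg/day. One extra participant at 3.0 × 25 = 75 to 4.5 × 25 = 112.5 mg/day in the TOPP-Trauma arm cancels it. At 50 per arm the dose needed is 150 to 225 mg/day.

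**3. Closed-form check with no maintenance users.** Let users' MED be lognormal with median 20 mg/day and log-SD 0.8.

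- Mean among users: 20 × exp(0.32) = 27.5. Arm means: 0.35 × 27.5 = 9.6 and 0.20 × 27.5 = 5.5. Difference: 4.1.
- Second moment among users: 400 × exp(1.28) = 1,439. Variances: 0.35 × 1,439 − 9.6² ≈ 411 and 0.20 × 1,439 − 5.5² ≈ 257.
- Standard error at 25 per arm: √((411 + 257)/25) = 5.2. Then 4.1/5.2 = 0.80, a wrong-sign probability of about 21%. Simulation gives 20%.

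**4. Simulation when the benefit is cessation.** 25 per arm, 40,000 trials per scenario. Users are as in step 3. Maintenance users are 0%, 4% or 8% of each arm, at a median of 90 or 150 mg/day (log-SD 0.4). Ranges run over the maintenance settings.

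| Still using, control vs TOPP-Trauma | Mean has wrong sign | Opioid-free % has wrong sign | Sign reverses without 1 participant | Without 2 | Mean and % point opposite ways |
|---|---|---|---|---|---|
| 35% vs 20% | 20-38% | 9% | 28-40% | 47-65% | 13-28% |
| 35% vs 25% | 29-42% | 17% | 34-41% | 56-67% | 16-26% |
| 60% vs 45% | 26-38% | 11% | 30-38% | 49-62% | 18-29% |

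The removal columns take out the highest values in the arm with the higher mean. They measure fragility, not error. With no maintenance users at all, the removal figures are still 28-34% (one) and 47-56% (two).

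**5. Other sample sizes.** At 20 per arm (25 less the 20% attrition that Table 3 accepts), removing one reverses the sign in 31-43% and removing two in 51-69%. At 50 per arm the figures are 18-34% and 32-58%.

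**6. Simulation when the benefit is a lower dose.** 25 per arm, users' median 15 mg/day under TOPP-Trauma vs 30 in control, log-SD 0.8.

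| Still using | Wrong sign: mean | Share still using | Mann-Whitney |
|---|---|---|---|
| 35% in both | 13% | 44% | 34% |
| 35% in both, plus 4% maintenance users | 22% | 44% | 36% |
| 60% in both | 5% | 44% | 15% |
| 35% control vs 30% TOPP-Trauma | 9% | 30% | 24% |

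Here the ranking is the reverse of step 4.

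**7. Overall median.** With 25 per arm the median is 0 when 12 or fewer are using. At 35% vs 20% using, both medians are 0 in 94% of trials (84% when 8% maintenance users are added).

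**8. Setting aside participants chronically prescribed opioids before injury.** The wrong-sign rate of the mean falls from about 34% to 21% under cessation with 8% maintenance users, and from about 23% to 13% under dose reduction with maintenance users present. This step helps under both kinds of effect.

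**The case against.** The strongest reply has four parts.

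- **The robust summary is already planned.** The opioid-free percentage is in the very next sentence. This stands: a reader might infer that the article judges opioid use by the mean alone, and it does not. What is missing is the role of the percentage in judging direction.
- **Replacing the mean could be worse.** A reader might go on to infer that the share still using, the median or a rank comparison should take the mean's place. The documents do not support that. The program works by stepwise dose reduction at each session, and some patients are not expected to reach zero. If its effect is on dose and not on cessation, step 6 shows the share and ranks doing worse than the mean. Step 7 shows that the overall median would usually say nothing if about a third or fewer still use opioids.
- **The percentages are assumed.** True. The influence arithmetic in step 1 needs only a dose and n, and step 4 does not need maintenance users to show fragility, but the exact rates should not be read as predictions.
- **This is a pilot.** The Sample Size section disclaims statistical power, the objective is to describe, and no test, threshold or progression rule uses the sign of mean MED/day; the numeric criteria in Table 3 concern feasibility. A reader might infer that the trial risks a false efficacy conclusion. It does not, and much of the instability is simply small numbers. This limits the severity but does not explain why direction should rest on the mean without reference to the other planned summary.

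**Conclusion.** The point holds as a minor one. The article assigns direction and amplitude to means, and for MED/day at about 25 per arm one or two participants can set the sign of the mean difference. Under the assumed cessation effects the mean points the wrong way in 20-42% of trials and contradicts the opioid-free percentage in 13-29%. Under an assumed dose-halving effect the mean is the better guide (wrong in 5-22%). Neither summary is safe alone, and the documents do not show which kind of effect to expect.

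The figure of 25 per arm follows the abstract and Table 3 with an assumed 1:1 allocation. The Sample Size section's 50 in each group conflicts with these and must be reconciled. At 50 per arm the fragility is smaller but remains. The consequence is a fragile estimate carried into planning of the full trial.

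**What to change.** In the section on potential efficacy, for MED/day at 6 and 12 weeks:

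1. Keep the difference in mean MED/day as the total-dose summary, and show it with and without participants chronically prescribed opioids before injury. Define that group from pre-randomization information, never from follow-up dose, so that the restricted comparison is still between randomized groups. The full intent-to-treat mean stays.
2. Read the mean together with the planned opioid-free percentage and with the median and quartiles of MED/day among those still using. Add a Mann-Whitney probability as a supplement. The figures among users are descriptive, since who is still using may itself depend on the arm.
3. State a direction only when the mean and the opioid-free percentage agree. Otherwise report the direction as undetermined.

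Separately, make the abstract, Table 3 and the Sample Size section give the same number of participants.

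The cost is two or three sentences and no new outcome data. The downside is that direction will more often be undetermined. In the cessation scenarios the two summaries point opposite ways in 13-29% of trials; ties in the percentage come on top (for 35% vs 20% with no maintenance users, 14.7% − 8.6% = 6.1%). Under a pure dose effect with 35% using in both arms it happens more often: the mean is right in 100 − 13 = 87% and the percentage, by symmetry, in at most 44%, so at least 87 − 44 = 43% of trials would be undetermined. For a pilot of this size that is an honest report, and the doses among users would then show where the difference lies.

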### Ethical Considerations

Procedures will be implemented to ensure that the information participants provide for this study will remain confidential. All participants will be assigned unique code numbers. Consent forms will be stored separately from the data. A master list, matching the names of participants with their study identification numbers, will be kept in a locked filing cabinet separate from the data. No names or other identifying information will appear in any data that is generated. Study findings will be presented in a comprehensive form and not linked to specific participants. All hard copies of the data will be stored in a locked filing cabinet in a locked office and electronic data will be kept in a computer secured with a password. Data will be stored for 10 years and then destroyed and treated as confidential waste or deleted from the research computer.

Protocol amendments will be communicated to the REB. Finally, the program is not known to be associated with any adverse events. However, if such events should occur during the study they will be documented.

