Based on positive preliminary findings associated with interventions aimed at reducing opioid consumption, we developed the Tapering Opioids Prescription Program for Trauma Patients at High Risk for Chronic Consumption (TOPP-Trauma). This program was adapted from a self-management intervention designed to prevent the acute to chronic pain transition in patients with major lower extremity trauma (iPACT-E-Trauma) [28–30]. This intervention focuses on the various dimensions of pain, pharmacological and non-pharmacological (i.e., cryotherapy, limb elevation, relaxation exercises) strategies for acute pain management, health promotion strategies, and a return to pre-injury activities. The activities included in the intervention are similar to those found in interventions based on the cognitive-behavioral approach – that is, education, problem-solving, graded activity, continued monitoring, and matching of learned self-management behaviors with real-life situations [28, 29].

iPACT-E-Trauma underwent preliminary testing in a trauma population at low risk for the chronic consumption of opioids (e.g., no pre-injury use of opioids or substance abuse, low ISS, no psychological vulnerability) [31]. Clinicians and patients gave a positive assessment of this intervention’s acceptability [28]. Furthermore, iPACT-E-Trauma was deemed feasible, [30] with achievable research methods [31].

In addition to the content and activities from iPACT-E-Trauma for the self-management of acute pain, TOPP-Trauma will integrate education about opioid misuse and patient monitoring, for those presenting risk factors for chronic opioid consumption after a traumatic injury. Before progressing to a full scale RCT, this study aims to determine the capacity to provide the components specific to TOPP-Trauma, and whether the research methods can measure the potential effects of this intervention on opioid consumption in particular.

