#### Program structure

TOPP-Trauma combines two 10-minute educational sessions within the week prior to hospital discharge, and a maximum of six 15-minute opioid tapering counseling sessions every two weeks following discharge (Table 1). A trauma case manager nurse, a nurse practitioner student or the trauma service pharmacist, who have more than five years of experience in caring for the trauma population along the acute continuum of care will provide the counseling sessions. These clinicians will receive a 4-hour training session by the principal investigator on the conceptual underpinnings of the program, the tools used in the study, and on how to deliver the program through role-play. Moreover, meetings will be held every two weeks between the PI and clinicians who will provide TOPP-Trauma until 10 patients will be recruited and until they will have provided the entire program in at least two patients.

**Table 1 Tab1:** TOPP-Trauma Sessions

Sessions	Timing of Delivery	Components
Educational - 1	The week prior to hospital discharge	- The various components of pain (introduction to the biopsychosocial dimensions of pain and how they negatively or positively influence pain experience)
		- How to assess pain intensity
		- Adequate use of analgesics prescribed
		- Need to taper opioids to prevent abuse and dependence
		- How to use cryotherapy
Educational - 2	The week prior to hospital discharge	- How to use deep breathing relaxation exercises
		- The need to stay active
		- How to establish objectives for staying active with the SMART^a^ procedure (establish an objective with the participant)
		- The influence of sleep hygiene on pain and the characteristics of an adequate sleep hygiene
		- The strategies to achieve adequate sleep hygiene
Counseling - 1	One week after hospital discharge	- Assessment of patient’s average pain intensity at rest and upon movement in the last 48 h
		- Follow up on activity objective
		- Assessment of analgesics taken over the last 72 h.
		- Assessment of non-pharmacological pain management strategies used over the last 72 h and underscoring the importance of using these strategies.
		- Providing information on how to gradually reduce the consumption of analgesics (e.g., 25% opioid dose reduction OR decrease frequency of opioid use, e.g., every 6 h instead of every 3–4 h OR before activities causing high-intensity pain) if pain < 4/10 and does not interfere with activities.

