The TOPP-Trauma educational session will be based on the information included in the pamphlet given to the control group. Counseling sessions will be initiated one week after hospital discharge, and will be discontinued when patients cease opioid use or when the maximum number of planned sessions has been reached. A Program Feasibility Evaluation Logbook will guide session delivery for the trauma nurse and the trauma pharmacist. The treating surgeon will be informed of the opioid tapering plan at the time of the participants’ appointment at the outpatient clinic, to ensure treatment consistency. The number (i.e., dose) and frequency of counseling sessions was determined based on the established timeline for transitioning towards chronic opioid consumption (i.e., 12 weeks) [2] and interventions tested in other high-risk populations. These reported a significant decrease in opioid consumption after five to six sessions [25, 26]. Considering that trauma patients admitted in the trauma center where the study will be conducted come from various regions, counseling sessions will either be provided over the phone or face-to-face at the outpatient clinic, at the time of the follow-up appointment with the treating surgeon. Counseling sessions will be delivered at the outpatient clinic whenever possible in order to concomitantly inform the treating surgeons on the opioid tapering plan.

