## Discussion

### Study contributions

Chronic opioid consumption has been identified in a significant number of trauma patients. To this day, no intervention with an adequate research design has been tested to provide high-level evidence-based guidance on how to address this issue. This pilot RCT will provide the required data on the feasibility and acceptability of TOPP Trauma in order to adjust the various features of this intervention before evaluating its effects. Moreover, findings will provide information on the research methods to evaluate the effect of TOPP-Trauma, while providing an adequate estimation of within and between group differences regarding the chronic consumption of opioids, setting the stage for a full RCT. Such research projects could provide trauma teams with scientific direction on how to support patients self-manage their pain while transitioning back into the community, and reduce the social burden associated with the long-term use of opioids.

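### Adverse events are documented if they occur, with no event question scheduled in either arm and up to four times as many post-discharge study contacts in the TOPP-Trauma arm

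*Protocol article*

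**What the plan says.** Adverse events appear in one place, the end of Ethical Considerations. The article first states that "the program is not known to be associated with any adverse events", then adds that "if such events should occur during the study they will be documented". It does not say who looks for events, when, or by what question.

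The rest of the article gives no event question either. Table 2 has rows for intervention feasibility, research-methods feasibility, acceptability, and a combined row for opioid dose, non-opioid analgesics and the Brief Pain Inventory; it has no adverse-event row. Under Data Collection, the research assistant's tasks at 6 and 12 weeks are opioid use, non-opioid use and the Brief Pain Inventory, plus a call to the community pharmacy. The Data analysis section names no event summary.

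Contact after discharge differs by arm. Under Program structure, the experimental arm has "a maximum of six 15-minute opioid tapering counseling sessions every two weeks following discharge", and these "will be discontinued when patients cease opioid use or when the maximum number of planned sessions has been reached". Controls receive a pamphlet before discharge and no guided sessions. The Blinding section says that the clinicians who deliver the program know the allocation and the research assistant does not.

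**The concern.** If events are written down when they surface, the number recorded depends on how often someone is there to hear of them. In this trial that opportunity differs by arm by design. At each counseling session an unblinded clinician asks about pain and analgesic use and completes a logbook that includes challenges met in delivery. An event mentioned there has a natural place to be recorded. A control participant has no matching occasion.

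The premise that no adverse events are known gives limited reassurance. The parent program "underwent preliminary testing in a trauma population at low risk for the chronic consumption of opioids". TOPP-Trauma adds tapering counseling, and its eligibility criteria admit people with pre-injury opioid use or substance abuse. Program Content foresees tapering "until patients chronically prescribed opioids reach their target maintenance dose", so some participants will already be on long-term opioids. The absence of known events in a different program and population says little about this one.

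At stake is whether any event counts the pilot reports by arm can be read side by side. An excess in the TOPP-Trauma arm could come from more contact, and a count of zero could mean only that nothing was volunteered.

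**Working it through.** **Reproducing the plan's own count.** Program structure gives "two 10-minute educational sessions within the week prior to hospital discharge" and at most six counseling sessions: 2 + 6 = 8, which matches S1 to S8 in Table 2. The two educational sessions come before discharge and are not counted below. From Table 1, counseling falls at weeks 1, 3, 5, 7, 9 and 11 after discharge.

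**Scheduled study contacts after discharge.** Both arms have two research-assistant contacts (Data Collection). The TOPP-Trauma arm also has c counseling sessions, with c from 0 to 6. The ratio is (c + 2)/2.

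| c | TOPP-Trauma | Control | Ratio |
|---|---|---|---|
| 0 | 2 | 2 | 1.0 |
| 1 | 3 | 2 | 1.5 |
| 2 | 4 | 2 | 2.0 |
| 3 | 5 | 2 | 2.5 |
| 4 | 6 | 2 | 3.0 |
| 5 | 7 | 2 | 3.5 |
| 6 | 8 | 2 | 4.0 |

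**Average ratio with early stopping (assumption).** Suppose everyone has the first session and a constant share s stops after each one. Mean sessions are the sum of (1 − s)^i for i = 0 to 5.

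- s = 0.1: 4.69 sessions, ratio 3.3
- s = 0.2: 3.69 sessions, ratio 2.8
- s = 0.3: 2.94 sessions, ratio 2.5
- s = 0.5: 1.97 sessions, ratio 2.0

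The Background says that use beyond 12 weeks affects up to 35% of trauma patients. Setting s so that 35% still use opioids at the end gives s = 1 − 0.35^(1/6) = 0.161, a mean of 4.05 sessions and a ratio of about 3.0. That 35% is an upper figure for trauma patients in general, so this is only an illustration.

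**What unequal contact could do to counts (assumption).** Suppose an event is present throughout follow-up and each contact reveals it independently with probability q. The chance that it is noticed is 1 − (1 − q)^k for k contacts: k = 2 in controls, 5 with three counseling sessions, 8 with six.

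| q | Control | TOPP-Trauma, c = 3 | TOPP-Trauma, c = 6 |
|---|---|---|---|
| 0.1 | 19% | 41% (2.2-fold) | 57% (3.0-fold) |
| 0.2 | 36% | 67% (1.9-fold) | 83% (2.3-fold) |
| 0.5 | 75% | 97% (1.3-fold) | 99.6% (1.3-fold) |

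The article gives no value for q, so the size is not known. The direction is the same in every cell.

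**After the fix.** Using only answers given at the two shared contacts, the ratio is 2/2 = 1.0 whatever c is.

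**The case against.** The strongest reply is that this is a journal article. Event definitions, forms and solicitation often sit in the full protocol, which is not shown, and the statement that events will be documented does not exclude active questioning. That stands to this extent: a reader might infer that nobody will ask, or that control-arm events are not covered because the sentence speaks of the program, and the article establishes neither. Silence alone would not be a finding. The point rests on a passive rule that is stated, together with a published schedule and task list that contain no event question and contact that is unequal by design.

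Second, the most direct foreseeable harm of tapering is poorly controlled pain. Pain intensity, pain interference and opioid use are measured at 6 and 12 weeks in both arms by a blinded research assistant, and pharmacy deliveries are collected in both arms too. This stands in full, so it would be wrong to say that harms in general are ascertained unequally.

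Third, four to one is not the typical ratio. Six sessions is a maximum, counseling ends at opioid cessation, and Study limitations says sessions and questionnaires will share a clinic visit where possible, so separate visits may be fewer. Surgeon appointments, where events could surface in either arm, are not in the count. This also stands.

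Fourth, no between-arm comparison of events is planned. The aims are feasibility and a description of potential efficacy, and Table 3 has no event criterion. A reader might infer that the decision on a full trial would be misled; nothing in the article ties that decision to event counts. It also does not follow that participants are left unwatched: tapering advice is conditional on pain relief, experienced clinicians deliver it, and the treating surgeon is told of the plan.

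**Conclusion.** The point holds in a limited form. As written, the plan would tend to find more events in the TOPP-Trauma arm, or few in either arm, for harms outside pain, pain interference and opioid use: for example withdrawal symptoms, overdose, unplanned emergency visits and readmission. Any counts of such events reported by arm would not be comparable.

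The imbalance in scheduled post-discharge contacts is at most 4.0 and falls to 2.5 with three counseling sessions and 1.5 with one. How far this would distort counts cannot be derived from the article; the detection figures above rest on an assumed chance per contact. The conclusion assumes that the published schedule and task list are complete on this point. If the full protocol already has the research assistant ask both arms the same event questions, the matter is closed by saying so.

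It is worth acting on because the article itself says of earlier work that "no intervention with an adequate research design has been tested", and because the means of equal ascertainment are already in place.

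**What to change.** Add one row to Table 2: a short event checklist, identical in both arms, asked by the blinded research assistant at 6 and 12 weeks. It could cover withdrawal symptoms, overdose, and unplanned emergency visits or readmission. Each time, ask about the period since the previous research-assistant contact (at 6 weeks, since enrollment), so that the window does not depend on counseling. Add the same item to the research assistant's tasks under Data Collection.

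Under Data analysis, state that any description of events by arm uses these answers only, and that events noted at counseling sessions are listed separately. In Ethical Considerations, replace the present sentence with a reference to this procedure and say that it applies to both arms.

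The cost is a few minutes at two contacts that already take place and a form amendment. No extra visit or staff is needed.
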